### PRI group

The PRI protocol provides RT for 45 min and IOT for 45 min. The PRI group will start from the Bi-Manu-Track proximal mode (i.e., forearm RT) and then the distal mode (i.e., wrist RT). In every session of RT, the patient will practice bilateral passive range of motion exercise, in which the unaffected side assists the affected UE, and bilateral active range of motion exercise. RT will be followed by IOT.

The IOT will be delivered according to the participant’s motor ability, namely, the Arm BASIS training (focusing on basic motor control) for severe arm paresis and Arm Ability training (focusing on complex motor control) for mild arm paresis [12]. Participants who score less than 35 in the baseline UE-FMA subscale and cannot achieve a precision grip will be assigned to the Arm BASIS training, and the other participants will receive the Arm Ability training [12].

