### Statistical analyses

The Student *t* test and *χ*^2^ will be used to analyze differences in baseline characteristics and outcome measures between the two groups. Two-way repeated-measures of analysis of variance will be used to determine the intervention effects. The within-subject factor is time (i.e., pretest, posttest, and follow-up assessment), and the between-subject factor is group (i.e., PRI and DRI). A post hoc Tukey test will be used when a group × time interaction or a main effect is observed. An *α* level of .05 is set for all statistical comparisons. Partial eta squared (*η*^2^) will also be estimated to determine the group difference for each outcome measure. Predictors of PRI and DRI outcomes will be estimated with the chi-square automatic interaction detector (CHAID) method. Data analyses will be performed using SPSS Statistics 18.0 software (IBM Corp, Armonk, NY, USA).

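### An unspecified main effect opens post hoc tests in an ANOVA that has the pretest among its outcomes; PRI against DRI should rest on a named, baseline-adjusted contrast

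*Protocol article*

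**What the plan says.** All of this is in the Statistical analyses section of the protocol article.

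- The model and its purpose: "Two-way repeated-measures of analysis of variance will be used to determine the intervention effects".
- The factors: "The within-subject factor is time (i.e., pretest, posttest, and follow-up assessment), and the between-subject factor is group (i.e., PRI and DRI". The pretest is therefore part of the response, not a covariate.
- The follow-on rule: "A post hoc Tukey test will be used when a group × time interaction or a main effect is observed". Which main effect is meant is not stated.
- The error level: "An *α* level of .05 is set for all statistical comparisons".
- Partial eta squared "will also be estimated to determine the group difference for each outcome measure".
- The Student t test and χ² "will be used to analyze differences in baseline characteristics and outcome measures between the two groups". No baseline-adjusted model is named.

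The Background states two kinds of hypothesis. Both groups are expected to improve and to keep the improvement, which is a question about time. PRI is expected to do better proximally and DRI distally, which is a question about group, with a direction.

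**The concern.** In a randomised comparison, the pretest difference between groups is chance. A group main effect averaged over three visits gives that chance difference a weight of one third and dilutes the treatment effect by the same share. The interaction does not have this fault, because it compares change. The rule nevertheless lets a main effect open post hoc testing on the same footing as the interaction, without excluding group. If group is included, each outcome has two routes to an apparent PRI–DRI difference, each at 0.05, and one of them is a poor estimate of the treatment effect.

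The planned output is also thin for the question asked. Partial eta squared has no sign, and an omnibus F test does not say at which visit, or in which direction, the groups differ. Tukey adds nothing after a group main effect, because there are only two groups. In a trial of 40 patients, the analysis should give a directional estimate with its precision.

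**Working it through.** **Inputs.** From the article: 20 per group, three visits, α 0.05 (taken as two-sided). The article gives no effect size, SD, correlation or power, so there is no planned figure to reproduce. Assumed: SD 1 at each visit, equal correlation ρ between visits, complete data, and an effect d at both later visits unless stated.

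**1. What the group main effect estimates.** With true differences 0, d, d at the three visits, the mean is (0 + d + d)/3 = 2d/3. For d = 0.80 this is 0.53; simulation gave 0.53 to 0.54.

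**2. What a chance baseline difference does.** Let the observed pretest difference be b with no treatment effect. The pretest contributes b/3, and each later visit is expected to differ by ρb. The main effect is then b(1 + 2ρ)/3. With b = 0.5 and ρ = 0.7 this is 0.5 × 2.4/3 = 0.40 SD, of which 0.5/3 = 0.17 comes from the pretest itself. In simulated trials with that imbalance, the main effect was significant in 11.8%. The change from pretest is off by (ρ − 1)b = −0.3 × 0.5 = −0.15 SD. The baseline-adjusted difference centres on 0.

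**3. Two routes per outcome.** If the two tests are independent, accepting either gives 1 − 0.95² = 9.75% under the null. A simulation of 20,000 trials at each ρ:

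| ρ | Group main effect | Interaction | Either |
|---|---|---|---|
| 0.5 | 5.0% | 4.9% | 9.6% |
| 0.7 | 5.1% | 5.0% | 9.9% |
| 0.8 | 5.2% | 4.9% | 9.9% |

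Each test alone holds its level over all randomisations. The excess comes from accepting either.

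**4. Power at d = 0.5.** Main effect: t test of 2d/3, variance (1 + 2ρ)/3, 38 df. Interaction: F with 2 and 76 df, noncentrality 20d²/[3(1 − ρ)]; for ρ = 0.7 this is 20 × 0.25/0.9 = 5.56. Adjusted contrast at postintervention: variance 1 − ρ², 37 df. Adjusted contrast averaged over both later visits: variance (1 + ρ)/2 − ρ², 37 df.

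| ρ | Group main effect | Interaction | Adjusted, postintervention | Adjusted, average |
|---|---|---|---|---|
| 0.5 | 24% | 34% | 43% | 59% |
| 0.7 | 21% | 53% | 58% | 73% |
| 0.8 | 20% | 72% | 73% | 86% |
| 0.9 | 19% | 96% | 94% | 98% |

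**5. Unequal effects over time (ρ = 0.7).**

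| Effect at postintervention / 3 months | Interaction | Adjusted, postintervention | Adjusted, average |
|---|---|---|---|
| 0.5 / 0 | 53% | 58% | 25% |
| 0.25 / 0.5 | 42% | 19% | 49% |
| 0 / 0.5 | 53% | 5% | 25% |

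The choice of contrast matters as much as the adjustment.

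**The case against.** The strongest defence is that the rule says only a main effect. The time main effect serves the stated hypothesis that both groups improve, and the interaction is named as a route to group differences. On that reading nothing is diluted. This stands in part: the text does not state that a group main effect counts as a treatment effect. It does not exclude it either, and the sentence on partial eta squared shows that group differences are to be drawn from this model.

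Several stronger criticisms are tempting but not supported:

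- *Patients with a missed visit are dropped.* That is how a classical repeated-measures ANOVA usually runs, but the article says nothing on missing visits, and a condensed article may leave this to the full protocol or SAP.
- *The planned analysis is biased and the adjusted one is not.* With complete data the group × time contrast is unbiased over randomisations (0.801 against 0.801 for the adjusted model at a true 0.80). A mixed model also has limits: with 15% of follow-up missing for reasons tied to the unseen value, it was off by 0.12 SD in simulation.
- *Tukey inflates error to 11–19%.* This needs a within-subject error term that the plan does not name, and it ignores that Tukey runs only after a significant test.
- *Adjustment always gains power.* It does not at high correlation with a single-visit contrast, nor when the effect falls elsewhere in time.
- *Leaving out the IOT programme is an error.* Both arms follow the same assignment rule, so it does not systematically confound the comparison.

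**Conclusion.** The point holds as a defect in a stated rule. With pretest in the response, a group main effect carries two thirds of a constant treatment effect plus one third of chance baseline imbalance. Treating it as an alternative to the interaction roughly doubles the false-positive rate per outcome, from 5% to about 10%. Both figures depend on reading the main effect as including group, which the wording permits but does not say. The 10% does not depend on an assumed effect size and varied little over correlations from 0.5 to 0.8.

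The gain in power from baseline adjustment is conditional. For 0.5 SD at both later visits and a postintervention contrast, it is about 9 points at correlation 0.5, 5 points at 0.7 and nothing material from 0.8. Averaging the later visits gains more if the effect is equal at both, and loses clearly if it is confined to one. The interaction test is valid, so the case for change rests on a clear, directional estimate and a single route to a group difference, with power as a possible benefit.

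**What to change.** 1. Compare PRI with DRI in a model with outcomes at postintervention and 3 months, and group, visit, group × visit and baseline value as terms.
2. Name one PRI minus DRI contrast in advance, at a stated visit or averaged over both, chosen by when the effect is expected. Report the adjusted mean difference with a 95% CI.
3. State that a group main effect including pretest is not evidence of a treatment effect, and drop Tukey for the two-group comparison.
4. Keep the time effect, reported as within-group change, for the hypothesis that both groups improve and maintain the improvement. The between-group model alone would leave that hypothesis without a test.
5. Adjustment for IOT programme (Arm BASIS or Arm Ability) is optional.

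The cost is a change of analysis wording, with no extra patients or assessments. The price is one degree of freedom, an assumption that outcome is linear in baseline, and lower power if the effect falls mainly at a visit other than the one named.

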This study is therefore designed to extend the previous study [12] by examining the effect of proximal (i.e., forearm first and wrist second) priority robotic priming and impairment-oriented training (PRI) and distal (i.e., wrist first and forearm second) priority robotic priming and impairment-oriented training (DRI) with a larger sample size (i.e., *n* = 20 in each group). We hypothesize that the PRI and DRI groups will both improve significantly on normalized muscle tone, sensorimotor impairment, upper limb function, self-efficacy, and quality of life from preintervention to postintervention and that the improvement will be maintained at the follow-up assessment. In addition, this study will compare the relative effects between PRI and DRI. We hypothesize that the PRI group will achieve better proximal UE motor ability and that the DRI group will achieve better distal UE motor ability.

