### Design and procedure

The study will use a single-blind randomized pretest and posttest design. Potential participants will be identified by the therapists or research assistants, and the study procedures, risks, and benefits will be explained. All participants will sign the informed consent before enrolling in this study and be allocated to the PRI or DRI groups based on a computer-generated random-sequence table (Table 1). The second author of this study ([name]) will generate the allocation sequence, enroll participants, and assign participants to interventions. Allocation concealment is ensured, as the computer-generated random codes are not released. The study will recruit 40 patients with stroke from hospital settings. Initial and outcome assessments will be administered by a well-trained and certified occupational therapist who is blinded to the group assignment, study hypotheses, and intervention of the patients. Trial participants, care providers, outcome assessors, and data analysts will be blinded after assignment to interventions. Unblinding is permissible when knowledge of the actual treatment is absolutely essential for further management of the patient.

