In clinical practice, therapists may use techniques targeting several joints of the UE in sequence to promote quality of motor control and functional use of the UE in daily activities. However, no studies to date have investigated the comparative effects of different sequences of training UE joints. Therefore, this study will attempt to extend the previous study [12] by comparing the two combined interventions (i.e., PRI and DRI). Results of this study may provide critical and empirical information about the effects of the training sequence of proximal priority (e.g., forearm first) and distal priority (e.g., wrist first) robotic priming before IOT on motor control and sensorimotor function of UE.

The limited research that is available regarding the effects of bilateral robotic priming combined with IOT provides no information about the responders who are more likely to benefit from this hybrid intervention. Therefore, another goal of this study will be to identify predictors of changes in outcomes after the interventions using the CHAID method. CHAID analysis builds a predictive model to help determine how predicting variables best merge to explain the outcomes in PRI and DRI. CHAID is based on the χ^2^ test to analyze structural linkages between variables and can potentially provide a mechanism for investigating the interaction between demographic and clinical features of patients and outcome measures [20].

Limitations of the design and implementation of this study must also be considered. This is a comparative efficacy study examining two parallel hybrid therapies (i.e., PRI and DRI) and, therefore, does not include a passive control or a conventional rehabilitation group. However, lack of an IOT-only group may limit this study from an estimation of the addictive priming effect of bilateral RT. The sample size of each group (*n* = 20) is small, which reflects the restriction of recruiting large samples of patients with stroke for efficacy studies.

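### CHAID on 40 patients (20 per arm) at an unadjusted .05 cannot support firm statements about who responds; label it exploratory and base the predictor analysis on a few pre-named predictors in one pooled model

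*Protocol article*

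**What the plan says.** The method is fixed in one sentence of Statistical analyses: "Predictors of PRI and DRI outcomes will be estimated with the chi-square automatic interaction detector (CHAID) method". The same section states that an α "level of .05 is set for all statistical comparisons". The Discussion makes this a study aim: "another goal of this study will be to identify predictors of changes in outcomes after the interventions using the CHAID method". It motivates the aim by saying that existing research "provides no information about the responders who are more likely to benefit from this hybrid intervention", and describes the method in general terms: "CHAID is based on the χ^2^ test to analyze structural linkages between variables".

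On size, Design and procedure states that "The study will recruit 40 patients with stroke from hospital settings", and the Background gives 20 per group. The Abstract names CHAID as the method for predictors of outcome, and the box on strengths and limitations lists it among the study's features. The end of the Discussion speaks of the need to identify responder characteristics and expects the findings to inform practice. The small sample is conceded as a general limitation, but not in connection with CHAID.

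**The concern.** CHAID tests every candidate predictor at each node and splits on the best one. The usual Bonferroni step within CHAID covers the merging of categories inside a predictor, not the choice among predictors. With α at .05 for each comparison, the chance of splitting on noise therefore grows with the length of the candidate list. Each split also divides an already small sample: from 20 patients, an even first split leaves 10 per node and a second leaves 5.

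The risk is that a split is reported as a responder characteristic and carried into practice when it is chance, while real predictors are missed. There is a second risk if a tree is grown in each arm. Two trees that look different invite the reading that different patients suit PRI and DRI, although nothing in them compares the arms.

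**Working it through.** **Inputs from the article:** 40 patients, 20 per arm; α .05 for all comparisons; CHAID. No false-split rate or power is stated for this analysis, so there is no figure to reproduce.

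**Assumptions:** k = 5 to 20 candidates per tree, one outcome, two-sided tests. The article gives no k. It lists 14 outcome instruments (4 primary, 10 secondary), and mentions demographic features, so the range is plausible but not documented.

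**Step 1. False first split in one tree.** With k independent noise candidates, each tested at .05, the chance is 1 − 0.95^k. This was checked by simulating the CHAID root split: quartile-binned predictors, merging of adjacent categories, Bonferroni within but not across predictors, minimum node 3 or 5, predictor correlation 0 to 0.5, and 300 runs per setting (Monte Carlo error about 3 points).

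| k | Formula | Simulated, n=20, continuous outcome | Simulated, n=20, median-split outcome | Simulated, n=40, either |
|---|---|---|---|---|
| 5 | 0.226 | 0.17–0.33 | 0.26–0.35 | 0.19–0.27 |
| 10 | 0.401 | 0.39–0.45 | 0.47–0.54 | 0.32–0.43 |
| 15 | 0.537 | 0.48–0.62 | 0.57–0.73 | 0.43–0.55 |
| 20 | 0.642 | 0.54–0.67 | 0.66–0.84 | 0.56–0.69 |

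By the formula, the rate is about 4 to 13 times the nominal 5% (0.226/0.05 = 4.5; 0.642/0.05 = 12.8). With a continuous outcome, 40 patients give about the same rates as 20. With a median-split outcome, pooling removes the small-sample excess and returns the rate to about the formula's level, no lower.

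**Step 2. When one tree passes 50%.** 1 − 0.95^13 = 0.487 and 1 − 0.95^14 = 0.512, so about 14 independent candidates are needed. In the simulation with a median-split outcome at n=20, about 10 are enough.

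**Step 3. One tree per arm.** The chance of at least one false first split in two trees is 1 − 0.95^(2k): 0.401 for k=5, 0.512 for k=7, 0.642 for k=10.

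**Step 4. Power for a real split within one arm.** For a 10 v 10 comparison (two-sided .05, noncentral t, before any adjustment), power is 0.19 at 0.5 SD, 0.40 at 0.8 SD, 0.56 at 1.0 SD and 0.72 at 1.2 SD.

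**Step 5. The alternative.** Three pre-named predictors give 1 − 0.95^3 = 0.143 unadjusted, and at most 0.05 with Bonferroni (0.05/3 ≈ 0.017 each). For a group × predictor term with a balanced binary predictor (four cells of 10), the standard error is √(4/10) = 0.632 SD. Power at .05 is 0.12, 0.23, 0.34 and 0.46 for interactions of 0.5, 0.8, 1.0 and 1.2 SD.

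**The case against.** The strongest reply is that a condensed article leaves the candidate list, node sizes, adjustment and validation to a fuller document, and that the figures above depend on exactly those settings. This stands in part: the missing list is no finding, and all rates here are conditional. It does not remove the point. The article itself fixes the method, the sample and α, makes prediction a goal, and nowhere marks it as exploratory.

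Several stronger readings are tempting, and the article does not support them:

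- *A single tree will more often than not split on noise.* This needs about 10 to 14 or more candidates. With 5 the rate is 17–35%.
- *The 20-patient arms cause the false splits.* The driver is the number of unadjusted candidates. Small numbers mainly cost power and stability.
- *Trees are certainly grown per arm.* The wording suggests it, but one pooled tree with group as a candidate also fits.
- *Change scores must be cut into responder classes.* CHAID can split a continuous outcome on F tests, and the article does not say that outcomes will be dichotomised. Its remark on the χ² test is generic.
- *The reported predictors will mostly be chance.* The calculation uses noise predictors only, so it cannot give the share of false findings among those reported.
- *The aim fails because the trees cannot show who does better on PRI than on DRI.* That is not the stated aim, which concerns responders to the hybrid treatment. The lack of an arm comparison is a caution about interpretation.

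**Conclusion.** The concern holds in a limited form. With 20 patients per arm and α .05 unadjusted across candidates, a tree's first split is noise with probability of roughly 20–80% for 5 to 20 candidates, when none of them is a true predictor. For two arm-specific trees, 7 independent candidates each already give about 51% for at least one false split. Power for a real 0.8 SD split is about 40%. A reported split is therefore weak evidence, and the absence of one says little.

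The analysis can be run to generate hypotheses, so it would be too strong to say that the predictor aim cannot be met. It cannot carry firm statements about responder characteristics, and differences between separate trees must not be read as differential response. The size rests on the assumed candidate count, on no adjustment across predictors, and on one outcome. Growing trees for several outcomes would add further chances of a false split.

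**What to change.** Make the main predictor analysis one pooled model (n=40) of the continuous outcome, adjusted for its baseline value and including group. Name two or three predictors in advance, with Bonferroni adjustment across them, and report estimates with 95% confidence intervals. Add group × predictor terms only if differential response is of interest. Label the whole analysis exploratory and word the conclusions to match. If CHAID is kept, present it as a descriptive display with a permutation p-value taken across all candidates and a cross-validated error.

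This changes analysis wording only, though the pooled model would be an addition to the planned repeated-measures ANOVA. The cost is that fewer predictors are examined and the claim is more modest. Power for interactions stays low: about 34% at 1.0 SD for a single test at .05, and less after adjustment. The pooled model therefore would not identify responders with confidence either; its gain is control of false predictor claims and a direct test of differential response if one is wanted.

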### Data management and quality

The documents of this study, including data recording sheets and signed informed consent forms, will be stored in a locked cabinet. The electronic database will be password-protected. Personal information of the participants will be deleted from the electronic database. The principle investigator ([name]) was in charge of data monitoring in this study. Therefore, there was no additional traditional data monitoring committee. The second author of this study ([name]) will conduct interim data analyses and the principle investigator ([name]) will make the final decision to terminate the trial.

### Adverse event monitoring and reporting

Pain and fatigue will be monitored during interventions because each session may last 90 min. Patients and the accompanying persons, if any, will also be instructed to report pain, fatigue, and any other adverse events whenever they happen. Adverse events will then be reported to the Ethical Committee for Human Research in accordance with the procedures of the National Taiwan University Hospital and the Feng Yuan Hospital of the Ministry of Health and Welfare, Taichung, Taiwan. Provisions, if any, for ancillary and post-trial care, and for compensation to those who suffer harm from trial participation followed the guidelines of the research ethics committees of the National Taiwan University Hospital and the Feng Yuan Hospital of the Ministry of Health and Welfare in Taiwan.

